#### Method 2: Ngene

Parallel to the Stata approach, a fractional factorial design was generated in Ngene using constraint specifications (the reject; property) to prohibit complete attribute-level overlaps across alternatives. After this initial design phase, systematic attribute overlaps were randomly introduced to mirror the balancing principles applied in Method 1, enhancing consistency between the two generation strategies.

#### Selection and finalization of the candidate set

After both candidate sets were constructed, a random selection was performed to reduce the set to 2,000 choice tasks to ensure computational feasibility during the optimization process in Ngene. From this reduced candidate set, Ngene selected the most suitable choice tasks according to efficiency and balance criteria.

#### Processing and preparation of the final design

The finalized choice tasks were structured and formatted in Stata to ensure a standardized, organized layout. The completed design was then saved in Excel format for seamless integration into the survey platform and subsequent fieldwork preparation.

We ultimately selected the design generated by Ngene due to its superior efficiency measures.

### Combining DCE and BWS to handle a large attribute number

Given the high total number of attributes and their distribution across four distinct DCE modules, a methodological approach inspired by Zhang et al. [44] was adopted. To compensate for missing data on attributes not included in each DCE, a BWS task type 1 was incorporated in which participants ranked all 31 attributes by their relative importance. This approach allowed inference of preferences across all attributes while maintaining a manageable cognitive load for respondents. To enable comparability between BWS importance scores and DCE utility differences, a scaling factor (𝑓(𝜃)) was calculated by leveraging attributes common to both methods.

The relative importance 𝐼_𝐾_ of an attribute 𝐾 in the BWS data was assumed to be proportional to the utility difference (Δ𝛽_𝐾_) in the DCE data, where Δ𝛽_𝐾_ = 𝛽_𝐾,max_ − 𝛽_𝐾,min_, and 𝑓(𝜃) is the estimated adjustment factor.

Combined estimation was performed using a joint likelihood function: 𝐿 = 𝐿_DCE_ + 𝜆 ⋅ 𝐿_BWS_, where 𝜆 represents the scale adjustment parameter accounting for differences in response variance between the elicitation formats.

By pooling the data into a joint model, the study aims to generate robust preference estimates across all attributes, overcome the traditional limitations of DCEs in handling large attribute sets, and improve the internal consistency and richness of the findings. This integrated approach is expected to provide a more comprehensive understanding of stakeholder preferences in digital health decision-making.

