#### Decision models of four value dimensions

A decision model defines the set of attributes relevant to the preference elicitation process in DCE. In this study, four decision models were developed based on literature, interviews and discussions. Each model reflects a specific value dimension, capturing stakeholder-relevant value contributions across the four domains: Impact on the Subject (e.g., clinical benefits, behavior changes), Impact on the Interaction (e.g., usability and interaction quality), Impact on the System (e.g., interoperability, efficiency, cost), and Impact on Society (e.g., sustainability, regulation, societal acceptance). A final set of 31 descriptive attributes were categorized into the dimensions as presented in Table 1 and Additional file 1. Each attribute was accompanied by a textual description and an icon to support visual comprehension.

Attribute levels were constructed using a standardized goal attainment framework, defining incremental improvements relative to a pre-digitalization status quo. Each attribute included five levels of achievement: 0%, 25%, 50%, 75%, and 100%. This consistent level structure supported comparability across attributes and value dimensions.

For visual differentiation of achievement levels, a viridis color scale [37], was applied to the associated pictograms. See Table 1. The viridis scale was selected to ensure accessibility for participants with color vision deficiencies and to avoid negative connotations associated with traditional color gradients such as red or yellow. This approach supported a perceptually uniform, inclusive survey design.

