### Partial profile design

To manage the large number of attributes and reduce cognitive burden, the study applied a partial profile design in the DCEs [41–43]. In each choice task (per decision model), participants are shown only a subset of the total attributes. However, across the full set of tasks, each participant will encounter all attributes. The visible attributes vary between tasks and are presented at different goal attainment levels. Attributes not shown in a given task are held constant at a goal attainment level of 75%, as explained to participants during the task introduction.

Per choice task, the Subject model displays 4 of 6 descriptive attributes, the Interaction model 5 of 11, and both the System and Society models 4 of 7, each supplemented by the two continuous attributes.

This approach reduces cognitive burden while maintaining attribute coverage and interpretability. This selective presentation mirrors real-world scenarios, where not all features are simultaneously salient for example, secure data exchange is critical for electronic health records, while user engagement matters more for behavior-change apps.

To preserve transparency, the survey displayed a complete attribute list in every choice task.

The use of a partial profile design allowed the study to balance realism, cognitive feasibility, and estimation efficiency. Detailed methodological specifications for attribute distribution, choice task construction, and randomization procedures are provided in Additional file 2.

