#### Explanations and contextualization

At the beginning of the survey, conceptual background based on the World Health Organization’s classification of DHIs [2] will be provided to support informed decision-making. Respondents will be introduced to four categories of DHIs: (1) patient and caregiver support (e.g., health promotion apps), (2) healthcare provider tools (e.g., treatment planning systems), (3) health management systems (e.g., resource planning), and (4) data services (e.g., data collection and analysis tools).

Before starting the choice tasks, participants will receive standardized definitions of all attributes and levels, supported by pictograms to enhance visual comprehension (see Table 1*)*. Participants will first be introduced to the specific value dimension to which they have been randomly assigned. This introduction includes a brief textual description of the dimension and detailed definitions of the associated attributes.

Two key concepts will be explained in advance to ensure consistent interpretation of the choice tasks. The ‘reference point’ (status quo) will be defined as the pre-digitalization baseline against which improvements are evaluated. ‘Goal attainment’ will be introduced as the level of improvement achieved relative to this baseline and operationalized through a structured percentage-based scale. To enhance intuitive understanding, a school grading analogy was described:

**0% – Insufficient**: No progress; requirements unmet.**25% – Sufficient**: Minimal improvement; significant deficiencies remain.**50% – Satisfactory**: Moderate improvement; around half of the goal achieved.**75% – Good**: Substantial improvement; minor gaps persist.**100% – Very good**: Full or surpassing goal achievement; no major deviations.

A sample choice task will then illustrate the structure and logic of the upcoming DCE tasks. All attribute descriptions relevant to the assigned dimension will be displayed again below each individual choice task.

After completing the DCE module, participants will receive short descriptions of the remaining three value dimensions. This step provides conceptual continuity and prepares respondents for the subsequent BWS Type 1 task, which includes all 31 attributes across all dimensions. During the BWS task, participants will see the full set of attribute descriptions to ensure informed comparisons across domains.

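### The BWS is described as asking for importance with no level range, yet its scores are tied to the DCE value of moving from 0% to 100%

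*Protocol article*

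**What the plan says.** The protocol article links the two instruments in *Combining DCE and BWS to handle a large attribute number*. The BWS is Type 1, so the objects being compared are attributes: "a BWS task type 1 was incorporated in which participants ranked all 31 attributes by their relative importance". The importance of an attribute "in the BWS data was assumed to be proportional to the utility difference" in the DCE, defined there as the coefficient of the highest level minus that of the lowest. One adjustment factor f(θ) makes the link; it "was calculated by leveraging attributes common to both methods". A second parameter, λ, "represents the scale adjustment parameter accounting for differences in response variance between the elicitation formats".

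The DCE range is set in *Decision models of four value dimensions*: "Each attribute included five levels of achievement: 0%, 25%, 50%, 75%, and 100" percent. It is the same for all 31 descriptive attributes.

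The BWS screens are described in *Explanations and contextualization*: "During the BWS task, participants will see the full set of attribute descriptions to ensure informed comparisons across domains". Levels are not mentioned at that point. Before the BWS, for the dimensions outside their own module, "participants will receive short descriptions of the remaining three value dimensions".

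**The concern.** A DCE utility range always belongs to a stated change in level. A Type 1 importance judgement belongs to one only if the question says so. Without a range, a respondent may rate how indispensable an attribute is in general, how far current care falls short on it, or how much a full improvement would be worth. Only the last of these is what the DCE difference measures.

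The attribute weights are a central objective of the study, and the joint model is the stated route to estimates across all 31 attributes. The BWS is there to fill in attributes that a respondent did not see in the DCE. If it measures something else, and by an amount that varies between attributes, the joint weights lie between two quantities and represent neither. *Limitations* concedes that the perceived reference point may vary between participants and may complicate the reading of goal attainment, but does not carry that caution over to the BWS link.

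**Working it through.** The plan gives no figure for this link, so there is none to reproduce. The check compares what each instrument measures with what the two parameters can correct.

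**Inputs.**
- Attributes per module (*Partial profile design*): 6, 11, 7 and 7. Sum: 6 + 11 + 7 + 7 = 31, which agrees with the stated total.
- Levels: 0% to 100% for every descriptive attribute.
- Link: importance I_K proportional to Δβ_K, with one factor f(θ).
- Joint likelihood: L = L_DCE + λ · L_BWS.

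**Step 1: what Δβ_K is.** If more goal attainment is preferred to less, the highest-valued level is 100% and the lowest is 0%. Δβ_K is then the value of the full 0-to-100% improvement.

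**Step 2: how much of the BWS lies outside a respondent's DCE.** Each person completes one module. The BWS attributes that this person has never traded off against levels number 31 − 11 = 20 (Interaction), 31 − 7 = 24 (System or Society) or 31 − 6 = 25 (Subject).

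**Step 3: what one factor can correct.** Write I_K = c · g_K · Δβ_K, where g_K is the ratio of what the respondent judged to the 0-to-100% value. For two attributes K and J:

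I_K / I_J = (Δβ_K / Δβ_J) · (g_K / g_J)

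- If g_K is the same for all attributes, the last term is 1 and f(θ) absorbs the difference completely.
- If g_K differs by attribute, relative weights are off by g_K / g_J. No single f(θ) removes this. λ does not either: it is one number for the whole BWS part, so it changes how strongly the BWS counts, not the ratio between attributes.

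**Step 4: illustration under assumed values.** Take 31 attributes with Δβ_K lognormal (log-SD 0.5), BWS importance equal to Δβ_K · exp(e_K) with e_K normal with mean 0 and SD s, and one factor fitted by least squares; 4,000 replicates for each s.

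| s (assumed) | Median absolute relative error in Δβ implied by the BWS | Rank correlation with true Δβ |
|---|---|---|
| 0 | 0% | 1.00 |
| 0.2 | 14% | 0.91 |
| 0.4 | 29% | 0.75 |
| 0.6 | 45% | 0.61 |

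The values of s are assumptions; the documents give none. The table concerns the value implied by the BWS alone. The joint estimates also use the DCE data, so it shows the mechanism and does not predict the error in the joint weights.

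**The case against.** **The BWS wording is not shown.** The article summarises the task in one clause, the attribute table is a missing figure, and full model specifications are referred to Additional file 3. The actual item could name a range. This stands. The absence of a range is read from the Type 1 format and the description of the screens, so the first step is to confirm the wording. The linking assumption, by contrast, is stated outright in the article.

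**Respondents share one frame.** All attributes use one goal-attainment scale. The baseline and the scale are explained before the DCE, and respondents work through the DCE on that scale before reaching the BWS. Some will carry the range over. This softens the problem, but it does not put the range into the question, and for 20 to 25 of the 31 attributes the respondent has made no choice on that scale.

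**The BWS is not the only bridge.** A reader might infer that the comparison across dimensions rests on the BWS alone. It does not. Out-of-pocket cost and daily time appear in all four modules, respondents are randomised to modules, and *Limitations* foresees scaling across experiments by marginal valuations. What remains true is that the BWS is the only comparison across dimensions within one person, and that it enters the joint likelihood directly.

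**A fourfold error is not supported.** The article says of the DCE that "Attributes not shown in a given task are held constant at a goal attainment level of 75" percent. A reader might infer that respondents then judge only the last 25 points, so that weights are off by up to 100/25 = 4. But that rule concerns attributes hidden in a DCE task, and nothing carries it into the BWS. If every attribute were read as 75% to 100%, then under linear utility g_K = 0.25 for all of them, and f(θ) would absorb it.

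**Proportionality is openly stated as an assumption inspired by a published approach, and DCE and BWS are also analysed separately.** Both are correct. Openness does not secure the assumption for this instrument, and the separate analyses supply the material for a check without specifying one.

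**Conclusion.** The concern holds in a conditional form. The article ties BWS importance to the value of a 0-to-100% improvement, while the BWS as described asks for importance with no stated range. Where general importance departs from that value by different amounts for different attributes, f(θ) and λ cannot correct it, and the joint weights combine two quantities.

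The size is unknown: the documents give no basis for the spread of the departures. The conclusion rests on two assumptions: that the item wording does not already name the range, and that respondents' departures differ between attributes. It does not follow that the joint weights are unusable. Every one of the 31 attributes appears in both instruments across the four modules, so proportionality can be tested from data already planned.

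**What to change.** 1. **Instruction.** Unless the BWS wording already does so, state that each attribute is to be judged as an improvement from 0% to 100% goal attainment. The cost is slightly more reading and a minor change to an instrument that has been pretested and ethics-approved; whether the committee needs to be notified should be checked.

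2. **Prespecified proportionality check, within each module.** Compare the joint model with one common factor against one with attribute-specific BWS parameters. Report the BWS-to-DCE ratio for each attribute with confidence intervals, and the rank correlation. Fix beforehand the zero point of the BWS scale on which the ratio is formed.

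3. **Consequence.** Fix in advance a tolerance for the ratios and the rank correlation. It should be a limit on size, because with about 1,000 respondents per module a significance test may flag trivial departures. It should not demand identical rank order, which sampling error alone could break among up to 11 attributes. If the tolerance is not met, present DCE and BWS weights separately, with the joint weights as secondary.

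Steps 2 and 3 need no new data. They remain worthwhile if the BWS screens can no longer be changed.

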### Sample size

The study aims to recruit a total of 4,250–4,300 participants across two stakeholder groups which will be randomly assigned to one DCE module. Sample size calculations were guided by Orme’s rule-of-thumb for DCEs, assuming an average task complexity of 9 choice sets, 3 alternatives, and 6–7 active attributes per task [45]. These estimates were validated through simulation-based standard error testing for key attribute coefficients, targeting a maximum standard error of 0.05 for main effects. A minimum of 500 participants per DCE module is required to ensure sufficient power to estimate main effects.

To enable robust exploration of subgroup differences based on health experience, professional background, and familiarity with digital health interventions, the study aims to recruit a minimum of 1,000 respondents per module.

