#### Statistical analysis

The primary analysis of DCE data will use Conditional Logit Models to estimate aggregate preferences under the assumption of homogeneous choice behavior, in line with established DCE guidelines [45–47].

Mixed Logit Models (also referred to as random parameter logit models) will subsequently be applied to account for unobserved preference heterogeneity at the individual level by allowing preference parameters to vary across respondents [47, 48].

To further explore heterogeneity, Latent Class Analysis will be used to identify discrete segments within the sample that share similar choice patterns. Unlike the mixed logit model, which assumes continuous preference variation, the latent class model assumes the existence of qualitatively distinct subgroups with shared preference structures [49, 50].

BWS responses will be analyzed using count analysis and multinomial logit models to estimate the relative importance of each attribute across the full set [44]. DCE and BWS data will be integrated using a joint likelihood framework, applying scale adjustment parameters to harmonize utility magnitudes across elicitation formats.

Attributes will primarily be coded using effects coding, enabling interpretation relative to grand means. Missing data will be handled through case-wise deletion for incomplete choice sets, with additional sensitivity analyses planned to assess the robustness of results.

All analyses will be conducted using Stata (Version 17.0, StataCorp) [51]. Model fit will be evaluated using information criteria (Akaike Information Criterion, Bayesian Information Criterion) and likelihood ratio tests, where applicable.

Data processing and analysis will adhere to GDPR regulations and institutional data protection standards, including secure storage, anonymization, and restricted access.

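### In the joint DCE–BWS objective, λ multiplies the BWS log-likelihood from outside, where it is a data weight and cannot be the scale parameter the text calls it

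*Protocol article*

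**What the plan says.** The protocol article, under 'Combining DCE and BWS to handle a large attribute number', introduces two quantities that both concern scale.

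- The first is f(θ): "a scaling factor (𝑓(𝜃)) was calculated by leveraging attributes common to both methods". Behind it stands a proportionality assumption about Δβ_K, the gap between an attribute's highest and lowest DCE coefficients: importance "in the BWS data was assumed to be proportional to the utility difference". The section describes f(θ) as a quantity obtained from the data; it "is the estimated adjustment factor".
- The second is λ, which appears as a multiplier in the objective: "Combined estimation was performed using a joint likelihood function: 𝐿 = 𝐿_DCE_ + 𝜆 ⋅ 𝐿_BWS". The text then assigns this multiplier its task: it "represents the scale adjustment parameter accounting for differences in response variance between the elicitation formats".

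The printed objective contains λ but does not show f(θ), and the section does not say how the two relate. It also does not say whether λ is estimated or fixed in advance.

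Under 'Statistical analysis', the two data sources are to be integrated by a joint likelihood, "applying scale adjustment parameters to harmonize utility magnitudes across elicitation formats". The BWS model is named there too: "BWS responses will be analyzed using count analysis and multinomial logit models". Full model specifications are referred to Additional file 3, which is not at hand.

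**The concern.** In a logit model, response variance acts through a factor on utility inside the choice probability. A respondent who answers one format more consistently than the other has larger utilities in that format, relative to the error term. Correcting for this means rescaling the utilities. A factor placed in front of the whole BWS log-likelihood leaves the BWS choice probabilities unchanged and only makes each BWS answer count λ times. The task given to λ and its place in the formula therefore do not match.

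Each respondent completes only one of four DCE modules, and the joint model is the stated way to pool DCE and BWS information over all 31 attributes. An analyst who programmed the formula as printed would not obtain the variance correction that the text promises. Depending on how λ is handled, the BWS data could drop out or carry an arbitrary weight.

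**Working it through.** The plan states no numerical result on this point, so there is no figure to reproduce. The argument is analytic; a small simulation illustrates it.

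**1. What λ does in the printed position.** Read L_DCE and L_BWS as log-likelihoods. Each BWS choice contributes λ·log P = log(P^λ), which is an observation weight. A scale parameter μ would enter as P_i = exp(μV_i)/Σ_j exp(μV_j). The two forms are not equivalent.

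**2. λ estimated.** At any β, dL/dλ = L_BWS(β). The BWS model is a multinomial logit, so every log-probability is below 0 and L_BWS < 0. With λ ≥ 0 the maximum is at λ = 0, and the BWS data leave the model. Without that bound, the objective rises without limit as λ goes to minus infinity. Neither case yields a usable estimate of λ.

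**3. λ fixed at a value other than 1.** Take a parameter informed only by the BWS part, with information I, and treat the BWS choices as independent.

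- Inverse-Hessian variance: 1/(λI).
- Actual (sandwich) variance: (λI)⁻¹·λ²I·(λI)⁻¹ = 1/I.
- The model-based standard error is therefore wrong by a factor 1/√λ: too small by √2 ≈ 1.41 at λ = 2, and too large by the same factor at λ = 0.5.

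Parameters that the DCE also informs are affected less. The values of λ are examples; the article gives none.

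**4. Raw likelihoods.** If L means likelihoods and not their logarithms, independent parts combine as a product, so the sum is not a joint likelihood. The derivative in λ would then be positive and λ would grow without bound.

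**5. Illustration.**

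- From the article: 9 choice sets of 3 alternatives ('Sample size': "assuming an average task complexity of 9 choice sets, 3 alternatives, and 6–7 active attributes per task"), 1,000 respondents per module ('Sample size'), and 6 descriptive attributes as in the Subject module ('Partial profile design').
- Assumed, because the article does not give them: full-profile tasks with linear level effects; 6 BWS sets of 4 attributes per person, best choice only; true Δβ of 2.0, 1.6, 1.2, 0.9, 0.6 and 0.3; a BWS-to-DCE scale ratio of 0.5 or 2.0. One BWS data set was simulated per ratio.

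Estimates of the largest Δβ (truth 2.0) with fixed λ outside and no scale factor inside:

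| True ratio | λ = 0.1 | λ = 0.5 | λ = 1 | λ = 4 |
|---|---|---|---|---|
| 0.5 | 1.889 | 1.743 | 1.669 | 1.566 |
| 2.0 | 2.110 | 2.433 | 2.617 | 2.916 |

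At λ = 1 the errors are (1.669 − 2)/2 = −17% and (2.617 − 2)/2 = +31%. Across this grid, λ only sets how far the estimate is pulled toward the BWS-scaled value.

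With λ estimated subject to λ ≥ 0, it went to 4.5e-09 (ratio 0.5) and 2.0e-08 (ratio 2.0), and the estimates equalled the DCE-only fit (largest Δβ 1.962).

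With a scale factor inside the BWS utilities and unit weights, it was estimated at 0.523 and 2.070, with the largest Δβ at 1.975 and 1.970.

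With that factor inside and λ fixed outside at 0.1 to 2, the factor stayed at 0.517–0.526 or 2.064–2.074. The inside factor does the scale correction, and λ remains a weight.

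**The case against.** The strongest reply is that f(θ) already handles scale. The article says that importance is only proportional to Δβ_K, with f(θ) estimated from shared attributes. If f(θ) sits inside L_BWS, the correction is made there, and the one-line formula merely leaves out the arguments of each term. The simulation supports this: f was recovered for every fixed λ tried. The full specification is in Additional file 3, and the wording under 'Statistical analysis' is compatible with a scale inside the utilities.

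Much of this stands, and it limits what can be concluded. Four stronger readings are tempting but unsupported:

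- *The BWS data will drop out.* This needs λ to be estimated. The article calls f(θ) estimated and never says so of λ.
- *The pooled estimates will be biased by a given percentage.* The distortions in the table assume no factor inside the BWS utilities, and scale ratios that the article does not give.
- *λ and f(θ) are two competing scale parameters and hence not identified.* Outside the log-likelihood, λ is not a scale parameter; with λ fixed, f was identified in every run.
- *The cross-dimension framework depends on this formula alone.* The BWS is also analysed on its own across the full attribute set. Cost and time, common to all modules, are used for cross-module comparison ('Continuous attributes to enhance cross-dimensional comparability'; 'Limitations').

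What does not stand is that the text is therefore sound. It assigns the variance role explicitly to λ, and λ cannot fill that role in the printed position. If the additional file holds a correct model, the article misdescribes it and still needs correcting.

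**Conclusion.** The point holds as a mismatch between a printed formula and the role the text gives to its parameter. As log-likelihoods, λ is a data weight: it corrects no variance difference and cannot be estimated from this objective. If it is fixed away from 1, it re-weights the BWS data and invalidates inverse-Hessian standard errors, should those be used; the article does not name its variance estimator. As raw likelihoods, the expression is not a joint likelihood at all.

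These conclusions rest on the logit form alone. The size of any bias cannot be derived from the article, because it depends on the BWS-to-DCE scale ratio and on where f(θ) enters; the simulated figures are illustrative only. The reach is the pooled DCE–BWS estimates across the 31 attributes. The primary conditional logit analysis and H₀₁ to H₀₄ do not use the joint objective.

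**What to change.** Replace the formula with LL = LL_DCE(β) + LL_BWS(μ·Δβ(β)). Both log-likelihoods have unit weight, and the BWS scale μ, which is then f(θ), is estimated inside the BWS choice probabilities. In addition:

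- Normalise the scale of one DCE module and let the other three differ, or test that they are equal. Different respondents answer the four modules, and 'Limitations' itself warns of inconsistent scaling between experiments.
- Drop λ, or relabel it as a fixed weight stated in advance, with sensitivity analyses over other values.
- Use a respondent-clustered (sandwich) variance, because the same people supply DCE and BWS answers.
- Check the proportionality restriction against free BWS utilities with a robust Wald test. An ordinary likelihood-ratio test does not suit clustered data.

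The cost is one corrected formula and a small change to the likelihood program. No new data are needed.
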